### Management of Infusion-Related Reactions and Local Injection Site Reactions

#### **Infusion-related Reactions Grade 1 or Grade 2:**

If the investigator assesses a Grade 1-2 IRR to be related to administration of study intervention, then the Dara-SC administration should be interrupted. When the participant's condition is stable, Dara-SC administration may be restarted at the investigator's discretion. Refer to the USPI for further details regarding continuation of Dara-SC administration.

If the participant experiences a Grade 2 or higher event of laryngeal edema, or a Grade 2 or higher event of bronchospasm that does not respond to systemic therapy and does not resolve within 6 hours from onset, then the participant must be permanently discontinued from Dara-SC treatment.

#### **Infusion-related Reactions Grade 3 or Higher:**

For IRR AEs (other than laryngeal edema or bronchospasm) that are Grade 3, the Dara-SC administration must be stopped, and the participant must be observed carefully until resolution of the AE or until the intensity of the event decreases to Grade 1, at which point the Dara-SC administration may be restarted at the investigator's discretion. Refer to the USPI for further details regarding continuation of Dara-SC administration.

If the intensity of the AE returns to Grade 3 after restart of the Dara-SC administration, then the participant must be permanently discontinued from Dara-SC treatment.

For IRR AEs that are Grade 4, the Dara-SC administration must be stopped, and the participant permanently discontinued from Dara-SC treatment.

#### **Recurrent Infusion-related Reactions:**

If a Grade 3 IRR (or Grade 2 or higher event of laryngeal edema, or a Grade 2 or higher event of bronchospasm) recurs during or within 24 hours after a subsequent Dara-SC administration, the participant must be permanently discontinued from Dara-SC treatment.

#### **Injection Site Reactions:**

In clinical studies, SC administration of daratumumab was associated with local injection site reactions, such as induration and erythema, in some subjects. The reactions usually resolved within 60 minutes. Local injection-site reactions should be managed per institutional standards.

Individual dose modification of Dara SC is not permitted. For managing Dara SC-related toxicities, either a dose interruption or a dose delay is recommended.

Daratumumab must be held if any of the following criteria below are met, to allow for recovery from toxicity, regardless of relationship to daratumumab:

- Grade 4 hematologic toxicity, except for Grade 4 lymphopenia;
- Grade 3 or higher thrombocytopenia;
- Febrile neutropenia;
- Neutropenia with infection, of any grade;
- Grade 3 or higher non-hematologic toxicities with the following exceptions:
  - Grade 3 nausea that responds to antiemetic treatment within 7 days
  - Grade 3 vomiting that responds to antiemetic treatment within 7 days
  - Grade 3 diarrhea that responds to antidiarrheal treatment within 7 days
  - Grade 3 fatigue that was present at baseline or that lasts for <7 days after the last administration of daratumumab
  - Grade 3 asthenia that was present at baseline or that lasts for <7 days after the last administration of daratumumab

Other than on Day 1 of a cycle, if any ‘within-cycle’ daratumumab and hyaluronidase-fihj administration does not commence within the prespecified window (see table 6-5 below) of the scheduled administration date then the dose will be considered a missed dose.. Administration may resume at the next planned dose date. A missed dose will not be made up.

Delay of Day 1 drug dosing in any given cycle should not result in a skipped dose but should lead to a delay of the entire cycle instead. A minimum of 4 days between daratumumab doses

must be observed. If a dose is delayed, then the dates of all subsequent doses must be adjusted. If a dose delay occurs, then blood samples should be collected on the actual day of study drug administration, not on the original scheduled drug administration day.

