#### **6.3.5.1 Daratumumab SC Dosing**

Daratumumab SC injection will be administered as follows:

- Cycles 1-2: Days 1, 8, 15, 22
- Cycles 3-8: Days 1, 15
- Cycles 9-24: Day 1

All daratumumab administrations will be in an outpatient setting. Subjects will receive concomitant medications as outlined in [Section 6.2.2](#).

Vital signs should be monitored extensively on Cycle 1 Day 1 before, and after the first administration of daratumumab. For all other administrations, vital signs should be measured before the start of injection and at the end of the injection. If the subject experiences any significant medical event, then the investigator should assess whether the subject should stay overnight for observation. If the subject has not experienced a significant medical event but is hospitalized overnight only for observation, then the hospitalization should not be reported as an SAE.

If an infusion-related reaction (IRR) develops, then the injection should be temporarily interrupted or slowed down. In the event of a life-threatening IRR (which may include pulmonary or cardiac events) or anaphylactic reaction, dara-SC should be discontinued, and no additional dara-SC should be administered to the participant. See Section 6.5.1 for instructions on the management of IRRs.

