#### **6.4 Instructions for Initiation of a New Cycle**

A new course of treatment may begin on the scheduled Day 1 of a new cycle if all of the following are met:

- $ANC \geq 1.0 \times 10^9/L$
- Platelet count  $\geq 30 \times 10^9/L$
- Any other study drug-related adverse event must have resolved to Grade 1 or baseline (see Appendix 2)
- Serum uric acid and creatinine concentrations must return to baseline prior to carfilzomib doses during Cycles 1 and 2

If  $ANC < 1.0 \times 10^9/L$  but  $> 0.75 \times 10^9/L$ , the start of a new cycle is at the discretion of the treating investigator

If these conditions are not met on Day 1 of a new cycle, the subject will be evaluated weekly, and a new treatment cycle will not be initiated until the toxicity has resolved, as described above.

If daratumumab, carfilzomib, or lenalidomide, or daratumumab are held for the remainder of the previous cycle or the new cycle is delayed due to residual toxicity on the planned Day 1 of the next cycle, then the new cycle will be started at 1 dose decrement.

If a delay of starting a new cycle is greater than 21 days, the subject should be discontinued from treatment, unless continuing treatment is mutually agreed upon by the site Lead Principal Investigator at the University of Chicago and the co-investigator at the treating institution.

Dexamethasone may be discontinued without the subject discontinuing study treatment.

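### Section 6.4's one-step dose decrement names no drug, is triggered by a daratumumab hold that cannot lead to a reduction, and conflicts with Table 6-6 for carfilzomib; 6.2.2 and Table 6-6 also differ on holding anticoagulation

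*Protocol*

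**What the plan says.** **Starting a cycle.** Section 6.4 opens: "A new course of treatment may begin on the scheduled Day 1 of a new cycle if all of the following are met". The platelet condition is at least 30 x10^9/L. Failing a condition means waiting: "If these conditions are not met on Day 1 of a new cycle, the subject will be evaluated weekly".

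**The decrement.** A later sentence in 6.4 gives the triggers. It lists daratumumab, carfilzomib and lenalidomide, then daratumumab again, and continues "or daratumumab are held for the remainder of the previous cycle or the new cycle is delayed due to residual toxicity". The consequence is "then the new cycle will be started at 1 dose decrement". No drug is named as the one to be reduced.

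**Daratumumab.** It is due on Day 1 of every cycle (Section 6.3.5.1, ending with "Cycles 9-24: Day 1"). Under Injection Site Reactions in Section 6.5.1.1: "Daratumumab must be held if any of the following criteria below are met". One criterion is "Grade 3 or higher thrombocytopenia", whatever its cause. A delay of Day 1 dosing "should not result in a skipped dose but should lead to a delay of the entire cycle instead". Sections 6.5 and 6.5.1.1 both rule out reducing daratumumab in an individual patient.

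**Partner drugs.** Table 6-6 acts only when platelets fall below 30 x10^9/L. Lenalidomide is then held and resumed one level lower. Carfilzomib, at 10-30 x10^9/L without bleeding, is held and restarted at its previous dose, on first and later falls alike.

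**Anticoagulation.** Section 6.2.2 makes prophylaxis a required concomitant medication. It stops all anticoagulation below 30,000/mm3, with active bleeding, or when there is a risk of a fall to Grade 3 thrombocytopenia. Table 6-6 stops prophylactic anticoagulation below 30 x10^9/L, until the count is back to 30 or more.

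**The concern.** A dose-reduction rule has to say which drug is reduced and when. The 6.4 sentence does not name the drug. One of its triggers concerns a drug that has no reduction levels, and for carfilzomib its result differs from the table written for platelet toxicity. Two sites with the same patient could therefore restart carfilzomib or lenalidomide at different doses, each citing the protocol. Section 6.5 sends departures from the protocol to the Lead Principal Investigator. That does not help when two sections state different doses and neither is marked as prevailing.

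Section 6.4 is also where a site looks to decide whether a cycle may start, yet it does not mention the stricter daratumumab platelet rule. On anticoagulation, a patient who has recovered above 30 x10^9/L may be restarted on prophylaxis at one site and kept off it at another.

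**Working it through.** This is a comparison of rules. The only arithmetic is the size of one dose step and a count of cycle starts.

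**1. The rules side by side**

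| Situation | Section 6.4 | Table 6-6 |
|---|---|---|
| Platelets fall to 10-30 without bleeding; carfilzomib held to the end of the cycle | One decrement, drug not named | Carfilzomib at previous dose; lenalidomide one level down |
| Day 1 count of 10-30 without bleeding; cycle delayed | One decrement, drug not named | Same as above |
| Daratumumab alone held to the end of the cycle for Grade 3 thrombocytopenia; count never below 30 | One decrement, drug not named | Neither partner drug reduced |
| Day 1 count of 30 or more but still Grade 3 | Start permitted; 6.5.1.1 delays the cycle | Neither partner drug reduced |

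In the first two rows, the decrement agrees with Table 6-6 if it is meant for lenalidomide and contradicts it if it is meant for carfilzomib. In the first row carfilzomib is itself a listed drug that was held, so the contradictory reading is the direct one. Neither row depends on any CTCAE limit.

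The third row shows the daratumumab trigger failing. In Cycles 3-8 daratumumab is due on Days 1 and 15, so a Day 15 hold can last to the end of the cycle. Section 6.4 then calls for a decrement, daratumumab cannot take it, and Table 6-6 gives no reason for a partner drug to take it.

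**2. The Day 1 band.** The protocol adopts CTCAE v4.0 but does not print its limits, so the upper Grade 3 platelet limit is an assumption. At 50, the counts that pass 6.4 but are held under 6.5.1.1 run from 30 to below 50 x10^9/L. At 40, they run from 30 to below 40. The band vanishes only if the limit is 30 or lower.

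**3. Size of one step from nominal dose**
- Lenalidomide (Table 6-3): 1 - 20/25 = 20%.
- Carfilzomib (Table 6-2): 1 - 27/36 = 25%.

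After a fall to 10-30 without bleeding, Table 6-6 already reduces lenalidomide, so only the carfilzomib 25% is in question. If the count never fell below 30, either step would be additional to Table 6-6.

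**4. How often it could arise.** New-cycle starts run from Cycle 2 to Cycle 24: 24 - 1 = 23 per patient completing treatment. This is a ceiling. Section 6.3.5 says there will be no new starts, so a patient already past Cycle 1 has fewer left. The protocol gives no rate of Day 1 counts in the band.

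**5. Anticoagulation.** Take a patient who has recovered to 35 x10^9/L without bleeding. Table 6-6 releases prophylaxis because 35 is above 30. Under 6.2.2 the numeric and bleeding triggers are off, but the risk trigger can still apply. If the Grade 3 limit is 50, that trigger acts at counts well above the stated 30.

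**The case against.** The strongest reply is that the rules can mostly be reconciled.

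- **Cycle start.** Section 6.4 is permissive and 6.5.1.1 is mandatory for one drug. A reader might infer that counts from 30 up to the Grade 3 limit leave sites free to start or delay. The documents do not support that: starting on time with daratumumab breaches 6.5.1.1, and delaying breaches nothing. This part of the reply stands.
- **Delay caused only by the daratumumab rule.** A reader might infer that such a delay cuts lenalidomide or carfilzomib. The decrement sentence follows the paragraph on failing the 6.4 conditions, so residual toxicity most naturally means failing one of them. A count of 30 or more passes the platelet condition. This also stands, and it agrees with Table 6-6.
- **Anticoagulation.** Both texts use 30 as the numeric hold, and 6.2.2 is broader because it covers all anticoagulation and adds bleeding and clinical risk. A site can hold under 6.2.2 without breaching the Table 6-6 row. That is fair, but the risk is undefined and the two texts give different release points for a required treatment.

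The reply does not remove three defects: no drug is named, daratumumab is expressly a trigger when held to the end of a cycle, and carfilzomib after 10-30 without bleeding has two possible restart doses.

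**Conclusion.** The point holds as a minor wording error with a bearing on dosing and safety. The 6.4 decrement cannot be carried out as written for daratumumab, and it conflicts with Table 6-6 for carfilzomib. The cycle-start rules have one compliant course, which is to follow 6.5.1.1, but 6.4 does not point to it. The 6.2.2 risk trigger can keep prophylaxis held after Table 6-6 has released it.

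The dose at stake is one step: 25% of nominal carfilzomib, or 20% of nominal lenalidomide where platelets never fell below 30. The number of patients affected is unknown, and 23 cycle starts per patient is an upper limit. The Day 1 band assumes a Grade 3 platelet limit above 30 x10^9/L; the carfilzomib conflict needs no such assumption. The primary endpoint, its test and the sample size are untouched.

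**What to change.** In Section 6.4:
- Delete daratumumab, in both places, from the decrement triggers.
- State that the decrement applies only to the carfilzomib or lenalidomide that was held or caused the delay.
- State that Table 6-6 governs for platelets and Table 6-7 for ANC. Table 6-7 also differs from a blanket decrement: after a first ANC fall below 0.75 x10^9/L it resumes lenalidomide at full dose.
- Add a cross-reference saying that the 6.5.1.1 platelet hold for daratumumab applies on Day 1 and delays the cycle even when the 6.4 platelet condition is met.

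In Section 6.2.2, replace the risk wording so that prophylactic anticoagulation is held below 30 x10^9/L or with active bleeding and resumed at 30 or more, as in Table 6-6. Add active bleeding to the table row. If the clinicians prefer another value, use that single value in both places.

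The clinicians should confirm the dosing content, since deciding that a daratumumab-only hold reduces no partner drug is a clinical decision. The cost is amendment text plus the usual approvals under Sections 13.3 and 13.3.1: consideration of the three companies, IRB and regulatory approval, and IRB approval at each affiliate site. No analysis or sample-size change is needed.

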**Table 6-5 Daratumumab Administration Window**

| Cycles  | Frequency             | Dose Held | Dosing Re-start                        |
|---------|-----------------------|-----------|----------------------------------------|
| 1 and 2 | Weekly (q1wk)         | >3 days   | next planned weekly dosing date        |
| 3 to 6  | Biweekly (q2wks)      | >7 days   | next planned biweekly dosing date      |
| 7+      | Every 4 weeks (q4wks) | >7 days   | next planned every 4 weeks dosing date |

If a dose is delayed, then the dates of all subsequent doses must be adjusted. Any dose hold of more than 14 days due to toxicity will result in permanent discontinuation of daratumumab. Dose holds of more than 14 days for other reasons should be discussed with the Lead Principal Investigator. If a dose delay occurs, then pharmacokinetic and pharmacodynamic assessments should be performed on the actual day of study drug administration, not on the original scheduled administration day.

For infusion-related reactions of any grade/severity, immediately interrupt the daratumumab infusion and manage symptoms. Management of infusion reactions may further require reduction in the rate of infusion, or treatment discontinuation of daratumumab as outlined below:

- Grade 1-2 (mild to moderate): Once reaction symptoms resolve, resume the infusion at no more than half the rate at which the reaction occurred. If the patient does not experience any further reaction symptoms, infusion rate escalation may resume at increments and intervals as appropriate ([Table 6-1](#)).
- Grade 3 (severe): If the intensity of the reaction decreases to Grade 2 or lower, consider restarting the infusion at no more than half the rate at which the reaction occurred. If the patient does not experience additional symptoms, resume infusion rate escalation at increments and intervals as outlined in [Table 6-1](#). Repeat the procedure above in the event of recurrence of Grade 3 symptoms. Permanently discontinue daratumumab upon the third occurrence of a Grade 3 or greater infusion reaction.

- Grade 4 (life threatening): Permanently discontinue daratumumab treatment.

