| Sample Size  | 
A total of 45 non-transplant candidates and/or transplant candidates who agreed to defer transplant will be enrolled.
                                                                                                                                                                                                                                                                                                                                                                                                                                                                                                                                                                                                                                                                                                                                                                                                                                                                                                                                                                                                                                                                                                                                          |
| Study Design | 
This study will be a multi-center, open-label, phase 2 study, enrolling subjects with newly diagnosed MM who require systemic chemotherapy.
 
Dose Schedule and Dose Levels
Dosing schedule is based on 28-day cycles.
 
Daratumumab
Daratumumab (1800 mg) will be administered by SC injection by manual push over approximately 3 – 5 minutes in the abdominal subcutaneous tissues in the left/right locations, alternating between individual doses. The volume of the SC solution will be 15 mL for the 1800 mg dose.
 
 
• Cycles 1-2: Days 1, 8, 15, and 22
 
• Cycles 3-8: Days 1 and 15
 
• Cycles 9-24: Day 1
 
 
Carfilzomib
 
 
- Cycle 1: Days 1 and 2: 20 mg/m^2 IV infusion
 
                                                                                                                                                                                                                                                                                                                                                                                         |

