### 6.3.4 Daratumumab IV Administration *(IV administration is discontinued and not available after the approval of version 7 of protocol dated February 20, 2023)*

Daratumumab can be administered by IV infusion or subcutaneous injection as assessed by the treating investigator. Method of daratumumab administration will be patient-specific and based on treating investigator's assessment.

Daratumumab (16 mg/kg) can be administered as an IV infusion. Each subject's dose will be calculated based on the subject's weight at Cycle 1 Day 1 rounded to the nearest kilogram. The dose of daratumumab will remain constant throughout the study, unless the subject's weight changes more than 10% from Cycle 1 Day 1. All infusions will be planned as outpatient visits. On daratumumab infusion days, subjects will receive the following medications 1 hour prior to infusion; however, premedication up to 3 hours before

the dose of daratumumab is permitted:

- oral antipyretics (acetaminophen 650 to 1000 mg)
- oral or intravenous antihistamine (diphenhydramine 25 to 50 mg or equivalent).

Daratumumab IV will be administered as follows:

- Cycle 1: 16 mg/kg weekly **OR** Cycle 1 Day 1: 8 mg/kg Day 2: 8 mg/kg, Day 8, 15, 22: 16 mg/kg
- Cycle 2: 16 mg/kg weekly
- Cycles 3-8: 16 mg/kg IV infusion every 2 weeks
- Cycles 9-24: 16 mg/kg IV infusion Day 1

The dilution volumes, initial infusion rates, and increment for the first, second, and subsequent doses are provided in Table 6-1. The first infusion, cycle 1, with a volume of 1,000 mL, takes approximately 8 hours or with a volume of 500 mL, takes approximately 4 hours; the second and subsequent infusions, with volumes of 500 mL, take approximately 4 hours. The maximum infusion rate for all infusions is 200 mL/hour for cycle 1 and any subjects experiencing a Grade 1 or greater infusion reaction. Beginning cycle 2, subjects without a Grade 1 or greater infusion reaction during cycle 1 may receive daratumumab over 90 minutes. Infuse at a rate so that 20% of the calculated dose is infused over the first 30 minutes (200 mL/hour). If tolerated, infuse the remaining 80% of the dose over 60 minutes (400 mL/hour), resulting in an estimated 90 minute infusion (total volume=500 mL). The supporting company may modify the infusion rates or the pre-infusion medications prospectively based upon the information collected to date from this and other studies.

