| Neurological Assessment                       | X                                   |   |   |   |    |    |    |                              | X                                  |   |   |    |    |    | X               |                 |
| Correlative Samples                           |                                     |   |   |   |    |    |    |                              |                                    |   |   |    |    |    | X  |                 |
| Bone marrow aspirate sample for MRD analysis  | X                                   |   |   |   |    |    |    | X                            |                                    |   |   |    |    |    | X               | X  |
| CT-PET                                        | X                                   |   |   |   |    |    |    |                              | X                                  |   |   |    |    |    | X               | X  |
| Adverse Events                                | Ongoing                             |   |   |   |    |    |    |                              |                                    |   |   |    |    |    |                 |                 |
| Concomitant Medications                                    | Ongoing                             |   |   |   |    |    |    |                              |                                    |   |   |    |    |    |                 |                 |
| Daratumumab                                   | X                                   |   |   |   | X  |    |    |                              | X                                  |   |   |    |    |    |                 |                 |

| PROCEDURES                                       | KRd + Dara Consolidation Cycles 5-8 |   |   |   |    |    |    |                              | KRd + Dara Maintenance Cycles 9-24 |   |   |    |    |    | End of Tx | LTFU            |
|--------------------------------------------------|-------------------------------------|---|---|---|----|----|----|------------------------------|------------------------------------|---|---|----|----|----|-----------|-----------------|

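### Table 6-5 moves daratumumab to every 4 weeks at Cycle 7, two cycles earlier than every other statement of the schedule in the protocol

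*Protocol*

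**What the plan says.** Section 6.3.5.1, which sets out the subcutaneous schedule now in use, gives "Cycles 3-8: Days 1, 15" and then "Cycles 9-24: Day 1". The synopsis agrees: "Cycles 3-8: Days 1 and 15", with Day 1 only afterwards. Section 6.3.4, on the discontinued intravenous route, has the same change point: "Cycles 3-8: 16 mg/kg IV infusion every 2 weeks", then Day 1 in Cycles 9-24. The calendar in Appendix 8, under the column group "KRd + Dara Consolidation Cycles 5-8", marks daratumumab on Days 1 and 15. Under the maintenance columns for Cycles 9-24 it marks Day 1 only.

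Table 6-5 differs. Its second row assigns two-weekly dosing to Cycles 3 to 6. Its third row starts at Cycle 7 with the frequency "Every 4 weeks (q4wks".

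The table is in current use. The missed-dose rule in Section 6.5.1.1 covers any dose other than Day 1 that "does not commence within the prespecified window (see table 6-5 below". A late Day 1 dose has its own rule in the same section: it "should lead to a delay of the entire cycle instead".

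**The concern.** A protocol should give one schedule for the study drug. Here a table that sites are told to consult disagrees with four other places about Cycles 7 and 8. By the dosing sections, the only dose in those cycles that comes under the missed-dose rule is Day 15. The table's last row implies that this dose does not exist.

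The two cycles come just before the end-of-Cycle-8 assessment of stringent complete response and MRD-negativity, which is the primary endpoint. A site that read its dosing frequency from the table would give less daratumumab than prescribed before that assessment. Anyone reviewing deviations would also have two standards for whether a Day 15 dose in Cycle 7 or 8 was due.

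**Working it through.** **Inputs.** Cycle length is 28 days (Section 4.1.2.1). The frequency bands are those of Section 6.3.5.1 and of Table 6-5. The protocol states no total number of doses, so there is no figure of its own to reproduce first.

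**Bands side by side (doses per cycle).**

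| Cycles | Synopsis, 6.3.4, 6.3.5.1, Appendix 8 | Table 6-5 |
|---|---|---|
| 1-2 | 4 | 4 |
| 3-6 | 2 | 2 |
| 7-8 | 2 | 1 |
| 9-24 | 1 | 1 |

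The counts in the middle column are those of the full-dose-per-visit schedule in Section 6.3.5.1. Section 6.3.4 states its Cycles 3-8 frequency as every two weeks, which in a 28-day cycle is the same as Days 1 and 15. The sources part only in Cycles 7 and 8.

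**Dose counts.** Total = sum over bands of (number of cycles × doses per cycle).

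- Dosing sections, through Cycle 8: 2×4 + 6×2 = 20. Through Cycle 24: 20 + 16×1 = 36.
- Table 6-5 bands, through Cycle 8: 2×4 + 4×2 + 2×1 = 18. Through Cycle 24: 18 + 16×1 = 34.
- Difference: 2 doses, namely Day 15 of Cycle 7 and Day 15 of Cycle 8. That is 2/20 = 10% through Cycle 8 and 2/36 = 5.6% through Cycle 24.

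**Hold window.** Table 6-5 gives more than 7 days in both the two-weekly and the four-weekly row, so the band error does not change the window in Cycles 7 and 8.

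**Restart after a missed Day 15 dose in Cycle 7 or 8.** On the two-weekly row the next planned date is Day 15 + 14 = Day 29, which is Day 1 of the next cycle. On the four-weekly row the next planned date is also Day 1 of the next cycle, Day 29. The difference is zero.

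**Held Day 1 dose.** Section 6.5.1.1 excludes Day 1 from the missed-dose rule that points to the table and delays the whole cycle instead. The band error therefore has no bearing on a held Day 1 dose.

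**The case against.** The best case for leaving this alone is that the intended regimen is not in doubt. Table 6-5 is headed as an administration window and sits in the toxicity-management section. Nothing tells sites to take the schedule from it. Section 6 sends them to Appendix 8 for the study calendar, and that calendar is right for Cycles 5-8, as are the synopsis and Section 6.3.5.1. A site would have to set all three aside to omit a dose. For the purpose the table does serve, its content for Cycles 7 and 8 gives the correct answer. The practical reach may also be small: Section 6.3.5 says there are no new starts, and the protocol does not show whether anyone is still in Cycles 7 or 8.

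All of this stands, and it is why the point is minor. It does not remove the contradiction, because the frequency stated in a current drug-administration table is still wrong for two cycles.

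A reader might go further and infer that the table also sets the wrong restart date. For a held Day 1 dose, the two-weekly row would resume 14 days later and the four-weekly row 28 days later. The text below the table makes a toxicity hold of more than 14 days a reason for permanent discontinuation, so the longer wait could look serious. The protocol does not support that reading. Neither row governs a Day 1 dose, since Section 6.5.1.1 delays the entire cycle, so the comparison is between two outcomes that the text already rules out. Correcting the bands would not change this either: the four-weekly row would still describe a Day 1 dose, now from Cycle 9.

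**Conclusion.** The inconsistency holds, and it is confined to the frequency bands. Table 6-5 ends two-weekly dosing at Cycle 6, whereas every other statement of the schedule ends it at Cycle 8. The hold window and the restart after a missed Day 15 dose are correct as they are.

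The size is two doses, 18 against 20 through Cycle 8 and 34 against 36 through Cycle 24. It arises only on the assumption that a site takes its frequency from this table against the calendar and dosing sections. The document gives no evidence that any site has done so.

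Because the affected cycles precede the primary assessment, a reader might infer a bias in the stringent complete response or MRD-negative rate. Nothing in the protocol supports an estimate of such an effect, and none is claimed. The prescribed regimen, the exact binomial test, its power and the decision rule are unaffected. Severity: minor.

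**What to change.** In Table 6-5, change the second band from 3 to 6 to 3 to 8 (every two weeks) and the third from 7+ to 9 to 24 (every four weeks). Leave the window and restart columns as they are. Send sites a short memo saying that Day 15 daratumumab is due in Cycles 7 and 8. The cost is two table cells and the memo, with no change to the regimen, sample size or analysis. If no participant remains in those cycles, the correction still gives deviation review a single schedule against which to classify past doses.
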